### Biological material

To ensure the appropriate amount of samples, the collection of three vials of fasting venous blood (T_0_ and T_1_) is planned from each participant: (1) 1.6 mL into a vacuum EDTA-coated tube for hematologic analysis; (2) 5 mL into a vacuum heparin-coated tube for biochemical serum analyses run by the Diagnostic Laboratory of the Municipal Hospital in Olsztyn; (3) 5 mL into a vacuum heparin-coated tube for serum analyses run at the IAR&FR PAS. The heparin-coated tubes with blood will be centrifuged at 3500 rpm for 10 min. The serum will be aliquoted and stored in Eppendorf tubes in an ultra-freezer (-80 ˚C) until further analyses (inflammatory cytokines, ELISA gut permeability biomarkers, oxidative stress parameters).

Fresh morning urine (T_0_ and T_1_) will be collected from each participant, divided into aliquots, and stored either at 4 ˚C until basic clinical assessment or in an ultra-freezer (-80 ˚C) until further analysis (VOCs, oxidative stress parameters).

Urine samples after home-made SAT will be gathered from participants before visits (T_0_ and T_1_) and transported to the IAR&FR PAS, where samples will be stored in an ultra-freezer (-80˚C) until further analysis.

Stool samples (T_0_ and T_1_) will be gathered by participants not later than 3 days before visits, kept in a domestic freezer (-20 °C), and transported frozen to the IAR&FR PAS, where samples will be divided into approximately 0.2-gram and 1-grem aliquots without defrosting, and stored in an ultra-freezer (-80˚C) until further analysis (SCFAs, VOCs and ELISA gut permeability biomarkers).

Skin biopsy specimens (T_0_ and T_1_) from PS participants will be collected from a psoriatic lesion area (different regions of lesion occurrence) and a non-lesion area (right lower quadrant of the abdomen), while from healthy individuals, a skin specimen will be collected at the right lower quadrant of the abdomen. The 4-mm punch biopsy will be performed using local anaesthesia (1% lignocaine). One biopsy specimen from each area will immediately be frozen in liquid nitrogen, then stored at -80 °C until further inflammatory response gene expression analysis; the second biopsy specimen of each area will be stored in paraformaldehyde until further immunohistological analysis.

**Fig. 2 Fig2:**
[figure not shown]
Schematic representation of study design and sampling

### Clinical characteristics

The plasma and serum specimens will be aliquoted. Complete blood count, selected biochemical blood parameters (creatinine, aspartate aminotransferase - AST, alanine aminotransferase - ALT, C-reactive protein - CRP), lipid profile (total cholesterol, HDL, LDL, triglycerides, and apolipoprotein A and B), fasting glucose and insulin, and glycated hemoglobin will be determined according to standard procedures in the outpatient clinic of the Municipal Hospital in Olsztyn (Poland).

In addition, participants will undergo an oral glucose tolerance test under specific conditions (overnight fasting, no vigorous physical activity, no alcohol consumption, and no taking pain medications). They will consume a 75-gram glucose dose solution dissolved in water. The capillary blood glucose (drawn from the fingertip with single-use lancets (Accucheck Safe, Roche Diabetes Care, Poland) will be tested at 0 (fasting glucose), 15, 30, 45, 60, 90, and 120 min after drinking the glucose solution using glucometers and diagnostic strips (Contour Plus Ascensia, Ascensia Diabetes Care, Poland).

A basic urine evaluation will be conducted according to standard procedure in the diagnostic laboratory of the Municipal Hospital in Olsztyn (Poland).

### Anthropometric indices and body composition

Before anthropometric indices determination, participants will be asked to empty their bladders, change into light clothing and take off their shoes to promote consistency between each measurement. Body height will be measured on a standard stadiometer (Seca, Hamburg, Germany). The body weight and composition will be assessed by bioelectrical impedance analysis (Tanita BC-418 analyser, Tanita Corporation, Tokyo, Japan). Parameters will be estimated using the standard prediction equations and software provided by the manufacturer. The waist (at the narrowest point) and hips (around the widest part) circumference will be measured by flexible measurement tape, and the waist-hip ratio (WHR) will be calculated by dividing the waist circumference by the hip circumference.

### Nutritional status

The nutritional status of study participants will be evaluated using a validated KomPAN questionnaire and a 3-day food record recall. The questionnaires will be filled out by participants using the paper-and-pencil method to avoid the interviewer’s influence.

### Metabolic rate

The resting energy expenditure will be measured by using indirect respirometry with a ventilated mask Cortex MetaMax 3B mobile device, in conditions of thermal comfort, under fasting conditions, and in the supine position. Ventilated mobile Breath-by-Breath systems comprise components to collect and mix expired air, measure flow rate, analyse gas concentrations (oxygen was analysed using paramagnetic analysers and carbon dioxide using infrared analysers), and pump air through the system. The test will be performed after the device has been calibrated. The measurement is performed for approximately 20 min. Determining the volume of oxygen and carbon dioxide enables the determination of respiratory quotients and the degree of utilisation of fat, carbohydrates and proteins in the body.

### Determination of the quality of life and physical activity

The quality of life will be assessed using the Quality of Life SF-36 questionnaire – the Polish version or the World Health Organisation Quality of Life Instrument-WHOQOL-BREF standardised questionnaire. Additionally, in PS participants, the Dermatology Life Quality Index (DLQI) will be assessed. The full Polish version of the International Physical Activity Questionnaire (IPAQ) will be used to determine participants’ physical activity.

### Immunohistological skin analysis

In each skin specimen from lesional and non-lesional areas from PS participants and skin specimens from healthy individuals, the level of tumour necrosis factor (TNF), interferon gamma (IFN-γ), interleukins (Il-17 A, Il-17 F, Il-12, Il-23, Il-8, IL-22, Il-35) (only in affected specimens) and the profile of γδ T cells (CD3, TCRγδ CD27, CD45RA, CCR6, IL-23R), subtype Vγ9Vδ2 (in both lesional and non-lesional skin specimens) will be determined.

### Expression of inflammatory response genes

RNA isolation and gene expression (real-time PCR): Total RNA will be extracted from skin biopsy specimens using commercially available kits for RNA isolation (Rneasy Fibrous Tissue Mini Kit, QIAGEN, Hilden, Germany). Complementary DNA (cDNA) will be synthesised from mRNA using the High-Capacity cDNA Reverse Transcription (Applied Biosystems by Thermo Fisher Scientific). Before reverse transcription, samples will be treated with DNase I (Life Technologies by Thermo Fisher Scientific). The expression of specific mRNA will be quantified with TaqMan Gene Expression Assays (Applied Biosystems by Thermo Fisher Scientific) on the 7900 Real-time PCR System or an ABI ViiA™ 7-Sequence Detection System (Applied Biosystems by Thermo Fisher Scientific). All the results will be normalised to housekeeping gene expression as an endogenous control. The real-time PCR will be performed in the Molecular Biology Laboratory in the Institute. This Core Facility provides the service and equipment required for gene expression analysis (7900 Real-time PCR System and ABI ViiA™ 7-Sequence Detection System (Applied Biosystems by Thermo Fisher Scientific).

### Inflammatory mediators and cytokines

The profile of cytokines in blood serum will be determined using a commercial Bio-Plex 200 array system (Bio-Rad). A wide range of cytokines (FGF basic, eotaxin, G-CSF, GM-CSF, IFN-γ, IL-1β, IL-1ra, IL-2, IL-4, IL-5, IL-6, IL-7, IL-8, IL-9, IL-10, IL-12 (p70), IL-13, IL-15, IL-17 A, ) and chemokines (IP-10, MCP-1 (MCAF), MIP-1α, MIP-1β, PDGF-BB, RANTES, TNF-α, VEGF) will be analyzed using dedicated assay kits (Bio-Plex Pro Human Cytokine 27-plex Assay, Bio-Rad Laboratories, Hercules, CA, USA). A fully integrated system will be able to provide accurate and reproducible assay results and comprises a 96-well fluorescent microplate reader with a dual-laser detector, software and validation, and calibration kits and assays. All measurements will be repeated in duplicate.

### Gut microbiota characteristics

The hyper-variable regions of the 16S rRNA bacterial gene (V3-V8) will be amplified with primers 337F 5’- GACTCCTACGGGAGGCWGCAG − 3’ and R1391 5’- GACGGGCGGTGWGTRCA − 3’. Bacterial libraries will be created using a Ligation Sequencing Kit 1D plus either Native Barcoding Expansion or a set of custom barcodes. Final libraries will be sequenced on a GridION X5 sequencer (Oxford Nanopore Technologies, Oxford, UK). All bioinformatic analyses will be performed on the Galaxy Europe platform using publicly available, version-controlled tools. The reads obtained will be filtered for their quality with fastp (v1.0.1 + galaxy2; average read quality ≥ 9 Phred quality score ) and length (minimum 800 bp). During the demultiplexing step, the removal of adapters (crucial for preparing the reads for alignment to a reference genome, as adapter sequences can interfere with alignment accuracy) and barcodes (to ensure that only the actual RNA sequences of interest are retained for each sample, preventing sample contamination) will be performed with Porechop (v0.2.4 + galaxy1). High-quality reads will be processed for taxonomic identification at the genus level by matching the NGS sequences with sequences deposited in the NCBI using Kraken2 (v2.1.3 + galaxy2) and Bracken (v3.1 + galaxy0). Compositional analyses will be performed using total-sum scaling or relative abundances, and multivariate statistics will be applied after centred log-ratio transformation to normalise the data. Alpha diversity will be assessed using the Shannon and Simpson indices, and beta diversity will be evaluated with Bray–Curtis dissimilarity, each with Krakentools (v1.2.1 + galaxy0). Finally, differential abundance will be tested with ANCOM-BC (v1.4.0 + galaxy0) and ALDEx2 (v1.26.0 + galaxy0).

### Concentration and profile of SCFAs

The concentration and profile of SCFAs in stool samples collected from participants will be analysed using gas chromatography (Agilent 7890 A, Agilent, Wilmington, DE, USA) with a flame-ionisation detector (FID) and a 7683B autosampler, after diethyl ether extraction [32]. External standards of acetic, propionic, butyric, isobutyric, valeric, and isovaleric acids will be applied, as well as 2-ethylbutyric acid as an internal standard. Analysis will be performed in triplicate.

### Functional multi-sugar gut permeability assessment

To assess whole gut permeability (gastrointestinal and colonic permeability), urine SAT samples will be collected from participants [31]. To assess small intestine permeability, the concentration of lactulose, rhamnose, and lactulose/rhamnose (L/R) ratio will be determined; to assess colonic permeability, the concentration of sucralose, erythritol, and sucralose/erythritol (S/E) ratio will be determined in urine samples with a high performance liquid chromatography (HPLC) gradient system (LC-10, Shimadzu, Japan) coupled with a refractive index detector (RID-6 A, Shimadzu, Japan). Urine samples will be thawed and diluted with deionised water, and ion-exchange resin will be added to eliminate sodium ions, then the samples will be centrifuged. If necessary, a filtration step will be carried out to remove proteins. Sugars will be identified and quantified based on the comparison of their retention time with the external standards. Freshly prepared standards of lactulose, mannitol, sucralose, and erythritol (in ACN/H_2_O, Sigma–Aldrich) and their calibration solutions will be applied during analysis. All measurements will be repeated in triplicate.

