### Multi-sugar absorption test

Before the check-up visits T_0_ and T_1_, all participants will complete the multi-sugar absorption test (SAT) [31]. They will be instructed to perform the test on a day off from work, one day before the scheduled check-up visits. Participants will be asked to follow pre-test restrictions: maintaining normal daily activities and typical dietary patterns, but 2 days before the test, avoiding consumption of sugars (sucrose, lactulose, sucralose, erythritol and rhamnose) present in the sugar mixture, as well as alcohol, caffeine, and spicy foods.

On the test day, after an overnight fast and morning bladder emptying, subjects will ingest a sugar mixture (containing 1 g sucrose (PA-01-0238-O, POL-AURA, Morąg, Poland), 1 g lactulose (PA-03-9831-C, POL-AURA, Poland), 1 g sucralose (PA-03-9213-C, POL-AURA, Poland), 1 g erythritol (E968, Hortimex Plus Sp. z o.o. Sp. K,. Konin, Poland) and 0.5 g L-rhamnose (PA-03-1712-C, POL-AURA, Poland)), freshly dissolved in 150 mL of tap water. They will then be instructed to collect urine in a tulip-type container over 12 h. During the test, they will be permitted to drink water (150–200 mL per hour) to maintain adequate urinary output, but will not be allowed to eat for the first 5 h. Participants will collect urine samples at three intervals: 2, 5, and 12 h after ingesting the sugar mixture, and record the urine volume at each interval.

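### The HPLC standards for the sugar absorption test list mannitol and omit rhamnose, so as written the lactulose/rhamnose ratio has no calibrated denominator

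*Protocol article*

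**What the plan says.** Two sections of the protocol article bear on this point.

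The section Multi-sugar absorption test describes the drink. It has five components: sucrose, lactulose, sucralose and erythritol at 1 g each, and "0.5 g L-rhamnose (PA-03-1712-C, POL-AURA, Poland"). The dietary restriction for the two days before the test covers the same five sugars: "avoiding consumption of sugars (sucrose, lactulose, sucralose, erythritol and rhamnose) present in the sugar mixture".

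The section Functional multi-sugar gut permeability assessment describes the urine analysis. For the small intestine, "the concentration of lactulose, rhamnose, and lactulose/rhamnose (L/R) ratio will be determined". For the colon, "the concentration of sucralose, erythritol, and sucralose/erythritol (S/E) ratio will be determined in urine samples". The instrument is an HPLC system with a refractive index detector. The basis of measurement is then stated: "Sugars will be identified and quantified based on the comparison of their retention time with the external standards". The next sentence names the standards, which also supply the calibration solutions: "Freshly prepared standards of lactulose, mannitol, sucralose, and erythritol".

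**The concern.** The list of standards does not match the list of sugars to be measured. A method that identifies and quantifies each sugar against an external standard needs a standard for every analyte. Here rhamnose, the denominator of the L/R ratio, has none, while a standard is prepared for mannitol, which nobody is given.

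The measure at stake is the only functional test of small-intestine permeability that the article describes. Improved barrier function is one of the steps in the stated hypothesis, between restored microbiota and reduced skin severity. The test is also demanding for participants: a day off work, an overnight fast and 12 hours of urine collection in three intervals, before both T0 and T1. A laboratory or a later reader working from the published method would not know how the denominator was obtained.

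**Working it through.** The plan states no figure that could be reproduced on this point, and no power or error-rate calculation applies. The check sets three lists side by side: sugars in the drink (section Multi-sugar absorption test), sugars to be determined in urine, and external standards (both from section Functional multi-sugar gut permeability assessment).

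| Sugar | In the drink | To be measured | Standard listed |
|---|---|---|---|
| Lactulose | yes | yes (L/R numerator) | yes |
| Rhamnose | yes | yes (L/R denominator) | **no** |
| Sucralose | yes | yes (S/E numerator) | yes |
| Erythritol | yes | yes (S/E denominator) | yes |
| Sucrose | yes | no | no |
| Mannitol | **no** | **no** | **yes** |

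1. Measured but without a standard: rhamnose only.
2. Standard listed but neither given nor measured: mannitol only. The word appears nowhere else in the article.
3. S/E has standards for both terms. L/R has one for its numerator only.
4. Sucrose is given without a standard, but it is not named as an analyte, so it adds nothing to the point.

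Could this be a matter left to a fuller laboratory document? The article does not leave it open. It names four standards for four analytes, and three of the four match, so the list reads as complete. The section on short-chain fatty acids likewise names each of its standards. The sentence is intact prose, with no sign of a broken table or a redaction.

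Could rhamnose be quantified some other way under the stated method? No other route is given. The section on metabolic dysfunction markers describes mass-spectral confirmation for volatile organic compounds, but nothing of that kind is described for the sugars.

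How many samples would be involved if the text were followed literally? The Sample size section plans 30 participants per randomised arm, so the ceiling is 2 × 30 = 60 patients at two visits, or 60 × 2 = 120 patient urine sets. With the approximately 25 evaluable per arm that the same section expects at T1, the figure is nearer 60 + (2 × 25) = 110. Healthy participants come on top; the article does not give their number.

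**The case against.** The strongest reply is that this is a one-word slip and not a choice of design. Rhamnose is named consistently everywhere else: in the drink, with its amount and catalogue number, in the list of sugars to avoid, as an analyte, and as the ratio's denominator. The trial already buys L-rhamnose for the drink. No section plans a lactulose/mannitol ratio. That reading is the most probable one and it stands. It does not remove the point, because nothing in the article corrects the sentence and a reader cannot tell from it whether rhamnose is calibrated.

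The reply also rightly limits the consequence:

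- The secondary outcomes listed under Study outcomes refer to permeability biomarkers in blood and faeces. The urinary sugar test is not named there, so L/R is a described assessment and not an explicitly listed outcome.
- The barrier hypothesis does not rest on L/R alone. The article also plans S/E, four serum markers (zonulin, iFABP, claudin-3, LPS) and four stool markers (calprotectin, β-defensin-2, α1-antitrypsin, sIgA).
- The PASI outcome and its analysis model do not use this measurement.

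Two stronger readings are tempting. A reader might infer that the L/R data will be lost for every participant. The documents do not support this: loss would require the laboratory to follow the standards list against its own named analyte, and the urine is to be kept at -80 °C until analysis. A reader might also infer that a lactulose/mannitol ratio will be reported instead. No text plans one. If one were reported it would not be interpretable, since mannitol is neither in the drink nor among the sugars to be avoided, so any mannitol in the urine would come from uncontrolled intake.

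**Conclusion.** The mismatch is real and certain on the text: as written, the L/R ratio cannot be quantified by the stated method because its denominator has no standard. It is an internal inconsistency, probably a drafting error, and it touches one of the two functional permeability ratios. If the text were followed literally, about 110 and at most 120 patient urine sets would be affected, plus those of the healthy group. S/E, the ELISA biomarkers, the PASI primary outcome, the sample size and the error rates are untouched.

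This rests on the standards list being complete as printed, which its four-for-four form suggests. Whether any data are actually at risk depends on laboratory practice, which the article does not show. Nor does it establish that no urine has yet been analysed: it gives no date for that analysis, and parts of the Methods (supplements, enrolment measurements) are already in the past tense.

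**What to change.** Reconcile the sections Multi-sugar absorption test and Functional multi-sugar gut permeability assessment so that the sugars given, the sugars measured and the standards agree. On the present text, that means naming L-rhamnose in place of mannitol in the standards and calibration solutions.

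Separately, have the laboratory confirm in writing that it calibrates for rhamnose before the stored test urine is analysed. If any urine has already been run, the confirmation should say which standards were used for it.

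The cost is one corrected sentence if rhamnose is already calibrated, and one additional reagent if it is not. Samples held at -80 °C and not yet analysed should remain usable. No change to the sample size, the outcomes or the analysis model follows from this correction.

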### Intestinal barrier permeability and integrity biomarkers

Selected intestinal barrier permeability and integrity biomarkers will be analysed using commercial ELISA kits in blood and stool samples. Before each analysis, the biological material will be thawed and pre-treated according to the procedures indicated in the ELISA kits manuals. In particular, before the extraction, stool samples will be mechanically homogenised.

Analysis in blood serum: zonulin, iFABP, claudin-3, bacterial lipopolysaccharides (LPS).

Analysis in stool samples: calprotectin, β-defensin-2, α1-Antitrypsin, sIgA. The planned research will be carried out using a microplate reader (Infinite M1000 PRO, Tecan, Austria).

### Metabolic dysfunction markers

The oxidative stress parameters will be determined in blood serum samples. The oxidative status of lipids will be analysed using assays of superoxide dismutase (SOD) activity, catalase activity (CAT), and photochemiluminescence for lipid-soluble antioxidants (PCL-ACL), whereas parameters of protein oxidation will be established according to reduced and oxidised glutathione (GSH and GSSG), and status of protein glycation marker- methylglyoxal (MGO) and glyoxal (GO) by HPLC method in urine. The planned research will be carried out using a Microplate reader (Infinite M1000PRO, Tecan, Austria) with UV-VIS and fluorescence modes, Photochem^®^ apparatus (Analytical Jena, Jena, Germany), an HPLC system with autosampler (LC-10, Shimadzu, Japan) and a fluorescent detector (RF-10AXL, Shimadzu, Japan).

The qualitative and quantitative analysis of VOCs will be determined in urine and stool samples by headspace solid phase microextraction (HS-SPME) coupled with gas chromatography (7890 A GC, Agilent Technologies, USA) and mass spectrometry detector (5975 C VL MSD, Agilent Technologies, USA) [33]. Analysis of microbial volatile patterns in stool samples allows characterisation of the gut microbiota metabolites. The analysis will be preceded by SPME, then the collected urine and faeces will be portioned into an appropriate number of vials capped with a PTFE septum and a crimp cap. The compounds will be identified by comparing spectra in the mass spectral library of the National Institute of Standards and Technology (2005), comparing retention times, and calculating linear retention indices relative to a series of alkanes (C_7_-C_40_) and with standards of VOCs. The planned research will be carried out using a gas chromatograph (7890 A, Agilent, USA) equipped with MS and FID detectors.

